**Fig. 2 Fig2:**
[figure not shown]
Population density in the Netherlands 2012

In the Netherlands, primary care during pregnancy is given by midwives, with obstetricians only involved in complicated pregnancies. Furthermore it is not uncommon for deliveries to occur in the home environment: between 2011 and 2013 approximately 20 % of births were at home [24]. Pregnant women have therefore been recruited through midwifery clinics from 2011 and onwards. Recruitment started in 2011 in Zwolle, after which Purmerend and Den Helder were added as locations. Recruitment in these latter locations is still ongoing, but was finished in Zwolle in 2013. To date over 300 mother-child pairs have been included. Women less than 12 weeks pregnant at their first visit to the clinic are preferred for inclusion, however women may also be included at later stages in pregnancy. They are considered eligible for participation if they are able to fill out questionnaires in Dutch. Decisionally incapacitated subjects are not asked to participate, and twin pregnancies are excluded.

Thus far eight midwifery clinics have been involved in recruitment. Of these, six are located in the area of Zwolle. Midwifery clinics are chosen based on the number of hospitals they cooperate with in the area. If transfer options are limited to one hospital, the clinic is eligible for participation, as this facilitates tracking of child births which do not occur in the home situation. In Zwolle, where recruitment is already finished, about one in fifteen women agreed to participation.

### Follow-up of subjects

Data from regular care provided by midwives and/or obstetricians is collected for information on women’s health during pregnancy. Further information on the period before and during pregnancy is collected by means of questionnaires, which are sent out to women at inclusion, and at the end of each trimester (4 weeks after birth for the last trimester). Follow-up of the child is done by youth healthcare organizations (at 1, 2, 3, 4, 6, 9, 12, and 18 months of age, according to standardized protocols [25]), which monitor growth and development of children as part of the Dutch health care program. Questionnaires are sent to the mothers when the children are 3, 6, 9, 12, and 18 months of age. Biological samples are collected at birth and in the first 2 months after birth. Furthermore a house visit is scheduled at 12 months of age to make an inventory of the home environment. An overview of the follow-up is given in Fig. 3.

**Fig. 3 Fig3:**
[figure not shown]
Sample collection and follow-up of main health outcomes within the LINC study

### Measurements

A complete overview of measurements during pregnancy and the first 18 months after birth is given in Table 1.

**Table 1 Tab1:** Measurements in LINC during pregnancy and the first 18 months after birth

Time	Exposure	Anthropometry	Behavioral and cognitive development	Determinants of exposure	Other (questionnaires)
1^st^ trimester of pregnancy		Weight (mother, and father)		Maternal diet before pregnancy (FFQ)	Demographics
		Length (mother and father)		Occupational and residential exposure	Previous pregnancies, fertility
					Allergies (mother and father)
					Lifestyle
					Mental state, stress (mother)
2^nd^ trimester of pregnancy				Maternal diet during pregnancy (food diary)	Lifestyle
					Mental state, stress
3^rd^ trimester of pregnancy		Weight (mother, 36 weeks of gestation)			General health, medication, family history
					Lifestyle
					Mental state, stress (mother)
					Social support (mother)
Birth	Cord blood	Birth weight			
	Placenta	Head and waist circumference			
	Vernix				
	Heel prick blood				
	Meconium				
	Urine (1^st^ week)				
Month 1		Weight and length	van Wiechen Scheme		
		Head circumference			
Month 2	Breast milk	Weight and length	van Wiechen Scheme		
		Head circumference			
Month 3		Weight and length	van Wiechen Scheme		Infant diet
		Head circumference			Second hand smoke exposure
					Mental state, stress (mother)
					Crying/sleeping pattern
Month 4		Weight and length	van Wiechen Scheme		
		Head circumference			
Month 6		Weight and length	van Wiechen Scheme	Occupational and residential exposure	Infant diet
		Head circumference			Second hand smoke exposure
					Mental state, stress (mother)
					Social support (mother)
					Crying/sleeping pattern
Month 9		Weight and length	van Wiechen Scheme		Infant diet
		Head circumference			Second hand smoke exposure
					Mental state, stress (mother)
					Crying/sleeping pattern
Month 12	Saliva	Weight and length	van Wiechen Scheme	Hand, back, and mouth wipe	Infant diet
		Head circumference	Child behavior (infant behavior questionnaire)	Dust sample	Child allergies
				Occupational and residential exposure	Second hand smoke exposure
				Hand-to-mouth behavior child	Mental state, stress (mother)
					Crying/sleeping pattern
Month 18			van Wiechen Scheme		Second hand smoke exposure
			Child behavior (child behavior checklist)		Mental state, stress (mother)
					Crying/sleeping pattern

All measurements are collected from the child, unless mentioned otherwise

#### Assessment of exposure

The aim is to assess perinatal exposure. For this purpose cord blood is collected from each participant at birth. Blood samples taken from the mother are not collected for the study, as women are allowed to enter the study during any stage of pregnancy. The latest moment of inclusion is just before birth, therefore this moment is most suitable to start collection of samples. Next to that, cord blood is considered a proxy for prenatal exposure and collection is non-invasive for both mother and child. To determine postnatal exposure, mothers are instructed to collect breast milk during 1 week, starting 4 weeks after birth. Use of a breast pump is allowed, and when used, the brand of the pump is provided by the participant. Timing of breast milk collection was decided upon after feedback in a pilot study, in which mothers indicated that collection any earlier after birth was uncomfortable. Furthermore, a small piece from the fetal side of the placenta is collected for epigenetic studies, as well as a sample of vernix and meconium. Parents collect a urine sample of the child during the first week after birth, however we will aim to collect multiple urine samples of the child during early childhood. Finally, at 12 months, a saliva sample of the child is collected.

Exposure to PCB-153, DDE, hexachlorobenzene (HCB), dioxins (CALUX), brominated diphenyl ether (BDE)-47, BDE-99, hexabromocyclododecane (HBCD), perfluorooctanesulfonic acid (PFOS), perfluorooctanoic acid (PFOA), and the secondary DEHP metabolites mono(2-ethyl-5-carboxypentyl) phthalate (MECPP), mono(2-ethyl-5-hydroxyhexyl) phthalate (MEHHP), and mono(2-ethyl-5-oxohexyl) phthalate (MEOHP) will be assessed in cord blood and breast milk. These chemicals will be studied in particular for their suspected obesogenic health effects [26]. Other chemicals will include organophosphates, carbamates, neonicotinoids, pyrethroids, and methylmercury. Some of these compounds, such as the carbamates and neonicotinoids, have not been studied frequently for their health effects in humans. As they are suspected neurotoxicants, they will be predominantly studied in context of child behavioral development. Additionally levels of resorcinol bis(diphenylphosphate) (RBDPP) and bisphenol A bis(diphenylphosphate) (BPA-BDPP) will be determined in the saliva samples as well as the indoor dust samples. These two flame retardants are used as alternatives for deca-BDE in TV or flat screen housings, as well as other electronic equipment. For standardization purposes, the same laboratory is used per compound. Samples which are thus far not used will be stored for additional analyses, and more compounds may be determined as the study progresses. Lab QA/QC procedures have been published previously [27].

#### Health outcomes

There are various parameters early in life which are indicators for development later in life. Birth weight for example is inversely associated with hypertension and type 2 diabetes in adulthood [28, 29], and both high and low birth weight have been associated with obesity [30, 31]. Rapid growth in infancy has been identified as an independent risk factor for childhood obesity [32, 33]. A recent study by Gittner et al. showed that children who were obese at the age of 5 years already had distinct body mass index (BMI) patterns before 12 months of age, with children who had a normal BMI at age five always having a lower BMI from age 6 months and onwards compared to children who were obese at age 5 years [34]. They furthermore showed that BMI patterns over time differed between male and female children. Childhood obesity has also been related to exposure to endocrine disrupting chemicals early in life. Several studies have observed positive associations with BMI for chemicals such as organochlorine pesticides (e.g. DDE, HCB) [7, 35, 36] and PFAAs [37], although results are not unambiguous [38, 39].

Also brain development is regulated and influenced by hormones, and especially thyroid hormones are known to be essential for normal embryonal and foetal neurogenesis [40]. EDCs are known to affect thyroid hormonal function in particular. Therefore disruption of hormonal function during specific time periods important for brain development may have many consequences and may amongst others have adverse effects on neurodevelopment. Positive associations for prenatal EDC exposure and autism spectrum disorders have been reported [41–44], however studies in this area are relatively scarce. For attention deficit hyperactivity disorder, study results seem to be more convincing of an association with early life exposure to endocrine disruptors [20].

Given the physiological processes which may be affected by EDC exposure, it was decided to focus on physical growth as well as neurodevelopment. These outcomes are partially monitored by youth health care centres, which determine child weight, height, waist, and head circumference, and which monitor cognitive development by means of the van Wiechen scheme [45]. Furthermore at 12 months, the Infant Behavior Questionnaire is administered [46], followed by the Child Behavior CheckList (CBCL) at 18 months [47]. An overview of data collected from the child regarding physical growth and behavioral development, and by whom, is given in Table 2.

**Table 2 Tab2:** Anthropometric and behavioral development data collection by research staff (RS), midwives, and youth health care (YHC)

Parameter	Recorded by			Age child
	RS	Midwives	YHC	
Weight		X	X	Birth, 1, 2, 3, 4, 6, 9, 12, 18 months
Length		X	X	Birth, 1, 2, 3, 4, 6, 9, 12, 18 months
Head circumference		X	X	Birth, 6, 12 months
Waist circumference		X	X	Birth, 6, 12 months
Cognitive development			X	Birth, 1, 2, 3, 4, 6, 9, 12, 18 months
Behavioral development (infant behavior questionnaire, child behavior checklist)	X			12, 18 months

All measurements are performed by trained and experienced staff. Furthermore midwives received a measuring tape as well as strict instructions on how to perform these measurements, including to what precision measurements should be done (e.g. for birth weight: to the nearest 10 g). Weighing scales are provided by the midwife and are calibrated daily. Youth health care organizations received similar instructions as the midwives regarding measurement of weight, length, waist, and head circumference. Furthermore validated questionnaires are used to ensure quality of the data.

#### Determinants of exposure

Exposure to chemicals occurs in part through diet [48]. However, diet is a factor which is relatively easy to control or change and may therefore be a potential pathway through which daily exposure can be decreased. This was for example shown by Rudel et al. [1] who observed a significant reduction after a ‘fresh food’ intervention, which implied that participants followed a 3 day diet containing no canned foods or foods packaged in plastic [1]. We therefore aim to assess the relevance of diet, and certain food groups in particular, in the contribution to the body burden of exposure for our population. Information on maternal dietary habits before pregnancy is collected by means of a food frequency questionnaire [49], which was validated for dioxin intake through diet [50]. This questionnaire is administered at the end of the first trimester. As pregnancy may be a period in which dietary patterns may change because women may want to adopt a more healthy lifestyle, women also fill out a 2-day food diary at the start of the second trimester.

Exposure to flame retardant chemicals specifically occurs mainly through inhalation and ingestion of contaminated house dust. Young children are more exposed to house dust than adults because of their different body composition and their specific behavior. Children have a lower body weight compared to their relative surface area and therefore have a higher intake of flame retardant chemicals. Moreover, children explore their environment with their hands and mouths, performing mouthing behavior, in which objects are touched with the mouth or objects are put into the mouth, increasing exposure to contaminated dust [51, 52]. Finally, children often play close to the floor, enhancing direct contact with house dust.

To assess whether dust is a relevant carrier for flame retardants and if it contributes significantly to exposure during early childhood, home visits are performed when the child is 12 months of age. During these visits a saliva sample is collected from each child, as well as a hand, back, and mouth wipe to assess how much dust accumulates on the surface of the body and can potentially be digested or absorbed through the skin. Furthermore an indoor dust sample from the home is collected. In these samples flame retardants will be measured. Next to that, a questionnaire is administered at the start of the study, and at 6 and 12 months after birth, to inquire about amongst others housing characteristics, furniture and characteristics of electronic devices. Information on cleaning patterns and use of certain products such as personal care products, but also use of pesticides in the house and in the garden, is collected through this questionnaire as well.

#### Effect biomarkers

Associations with health outcomes will be determined for each compound individually. However, the compound by compound approach is not an accurate representation of the mixture of chemicals we are exposed to, and fails to take into account that chemicals may interact and may potentially enhance or diminish the effects they would have individually. It may therefore be useful to study biomarkers of effect. These biomarkers should be able to reflect complex exposures as well as the accumulation of exposures over time [53]. They are furthermore able to relate cause and (health) effect. As we suspect these chemicals to be endocrine disruptors, hormone levels will be included as effect biomarkers.

Cord blood will also be used to determine various hormone levels, including leptin, adiponectin, ghrelin, insulin, cortisone, glucagon, insulin-like growth factor 1, and sex hormone-binding globulin. The Dutch National Institute for Public Health and the Environment is approached in order to obtain data on thyroid hormones (total thyroxine) as measured in the neonatal screening programme.

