### Statistical analyses

For all analyses effect modification of the outcome by gender will be checked, as the included chemicals disrupt the endocrine system, and in particular steroid hormones. Linearity of exposure markers and outcome will furthermore be checked due to suspected nonmonotonic dose-response associations [62]. Next to that, various methods will be considered for dealing with exposure values below the limit of quantification (LOQ), including replacement by LOQ/√2 [63], and multiple imputation [64].

In order to quantify the relation between exposure and BMI at the age of 12 and 18 months, we will use linear multilevel (mixed) models. These models take into account the dependency of repeated measures within the individuals. For each compound a separate model will be composed for weight, height, BMI, and head circumference. Exposure quartiles, time, and gender will be added to the models as fixed effects and a random effect will be added for subject. Various covariates, described in 2.5.1, will be tested and included in the model if significant (change in β-coefficient > 10 %).

To study the relationship between exposure and behavior at the age of 18 months, linear regression analyses will be conducted. Both syndrome and DSM-oriented scales from the CBCL will be used for analysis. Syndrome scales are: Emotionally Reactive, Anxious/Depressed, Somatic Complaints, Withdrawn, Attention Problems, Aggressive Behavior, and Sleep Problems. DSM-oriented scales are: Affective Problems, Anxiety Problems, Pervasive Developmental Problems, Attention Deficit/Hyperactivity Problems, and Oppositional Defiant Problems. The overall scales ‘Externalizing’ and ‘Internalizing’, and the total score were also used.

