#### Covariates

Potential covariates were selected based on literature. Weight and length of both parents are measured by the midwife at inclusion, approximately 10–12 weeks in pregnancy. Measurement of maternal weight is repeated at 36 weeks of pregnancy to determine gestational weight gain. Gestational age is determined by means of ultrasound. Birth weight is measured by a midwife or a nurse and is obtained from registries of the midwives.

Questionnaires are administered at inclusion and the start of the second trimester to collect information on education (having a bachelor or master degree, yes or no), birth date of the mother, parity, and maternal smoking (yes or no) and alcohol intake during the first trimester (drinks per week). At inclusion, fish intake (grams per day) is determined by food frequency questionnaire which includes both frequencies and portion sizes [49]. One month after birth another questionnaire is administered to inquire on the use of medication during pregnancy, including folic acid intake (yes or no).

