### Strengths and limitations

The LINC study is a prospective birth cohort, which is one of the main strengths. Data of the children within the study is already collected very early during pregnancy and though current follow-up is planned until the children are 18 months of age, long-term follow-up is required to proper study associations with growth and behavioural development in children. Approval for extension of follow-up until the children are 48 months of age has already been given, but it is likely that follow-up will be extended to later ages. Furthermore a large variety of data is collected, focussing on multiple aspects of child health including growth, behavior, and nutrition, as well as factors in the direct environment of the child such as parental wellbeing, health, lifestyle, and residential environment.

Biological samples are collected at various time points to complete the information on health and development from each child. A broad range of exposures is assessed within these samples, taking into account already frequently studied compounds such as PCB-153, DDE, and dioxins, but also relatively new groups of chemicals such as perfluorinated alkyl acids, phthalates, carbamates, and pyrethroids. This facilitates comparison with previous studies but also adds to the body of knowledge on less frequently studied compounds. Studies which have assessed such a broad range of environmental chemicals in a variety of samples from a prospective mother-child cohort have thus far been few. We will furthermore aim to look further than the compound-by-compound approach and to look at chemical mixtures, amongst others by studying biomarkers of effect.

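### The growth models take one compound at a time with no other compound as a candidate covariate, so an association seen for one compound may belong to a correlated one

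*Protocol article*

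**What the plan says.** In the protocol article, Effect biomarkers sets the unit of analysis: "Associations with health outcomes will be determined for each compound individually". Statistical analyses repeats it for growth: "For each compound a separate model will be composed for weight, height, BMI, and head circumference". The terms follow: "Exposure quartiles, time, and gender will be added to the models as fixed effects and a random effect will be added for subject". Further covariates enter under a 10% change-in-coefficient rule, from the list in the Covariates section. No other compound is on that list. The item closest to a shared exposure source is diet: "fish intake (grams per day) is determined by food frequency questionnaire".

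For behaviour the article says only: "To study the relationship between exposure and behavior at the age of 18 months, linear regression analyses will be conducted". Quartiles are not stated for that outcome.

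Effect biomarkers concedes that working compound by compound misrepresents the mixture and misses interaction. It then turns to biomarkers of effect, with this requirement: "These biomarkers should be able to reflect complex exposures as well as the accumulation of exposures over time". The markers chosen are hormones in cord blood, plus total thyroxine sought from neonatal screening. Strengths and limitations says the study will also "look at chemical mixtures, amongst others by studying biomarkers of effect". The study aims name multiple regression and multivariate analysis in general terms.

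**The concern.** A model with one compound estimates the association of that compound together with whatever travels with it. If two compounds share a source and only one affects growth, the other will also show an association in its own model.

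The article itself gives reason to expect co-occurrence. Assessment of exposure lists three metabolites of a single parent phthalate (MECPP, MEHHP and MEOHP, all from DEHP) among its markers, and Determinants of exposure names diet as a route for chemicals in general.

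The admitted limitation concerns mixture and interaction; confounding between compounds is not mentioned. Hormones do not help with that confounding. They are possible intermediates between exposure and outcome, they do not show which compound acted, and adjusting for them could remove part of a real effect. Being measured around birth, they also cannot reflect exposure through breast milk (collected from 4 weeks) or house dust (sampled at 12 months).

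At stake is the aim, in Strengths and limitations, of adding evidence on less-studied compounds beside PCB-153 and DDE. A wrong attribution would defeat that aim.

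**Working it through.** The article states no figure on this point to reproduce. The check has two parts: what the specified models contain, and how large the bias could be.

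**1. Contents of the growth model.** Fixed effects: quartiles of one compound, time, gender. Random effect: subject. Candidates: the Covariates list. No term for a second compound can enter from that list. Fish intake, if it passes the 10% rule, gives at most partial control of one shared source.

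**2. Size of the bias.** Inputs:
- SD of BMI at 12 months: 1.36 kg/m² (Sample size).
- r² of the causal compound: 0.05 or 0.11 (the two values in Sample size).
- Children with usable samples: n = 200 (Sample size).
- Correlation rho between compounds: **not given, assumed** from 0 to 0.8.

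Set-up: compound A is inert and compound B is causal. They are bivariate normal with correlation rho, and BMI is measured once. There are 2,000 simulated cohorts per setting. A is tested in quartiles (F test on 3 degrees of freedom, alpha 0.05), first alone and then with B in the model.

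| rho | r² = 0.05: A significant, alone | Spurious top-minus-bottom quartile difference (kg/m²) | r² = 0.11: A significant, alone | Spurious difference (kg/m²) |
|---|---|---|---|---|
| 0 | 7% | 0.00 | 5% | 0.00 |
| 0.3 | 9% | 0.22 | 16% | 0.34 |
| 0.5 | 20% | 0.38 | 41% | 0.56 |
| 0.7 | 36% | 0.54 | 73% | 0.80 |
| 0.8 | 47% | 0.61 | 84% | 0.90 |

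With B in the model, A is significant in 4% to 6% of cohorts at every rho.

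**3. Check by formula.** The mean of the top quarter of a standard normal is 0.3178 / 0.25 = 1.271, so the top-minus-bottom gap is 2 × 1.271 = 2.542. The spurious difference is rho × √r² × 1.36 × 2.542:
- rho 0.5, r² 0.05: 0.5 × 0.2236 × 1.36 × 2.542 = 0.39 kg/m².
- rho 0.5, r² 0.11: 0.5 × 0.3317 × 1.36 × 2.542 = 0.57 kg/m².

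Both agree with the simulation to within its error. For scale, Sample size calls a difference of 1.0 kg/m² relevant.

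**4. Cost of adjustment.** For a linear term and one co-exposure, variance rises by 1/(1 − rho²), so 200 children carry the information of 200 × (1 − rho²):
- rho 0.3: 200 × 0.91 = 182
- rho 0.5: 200 × 0.75 = 150
- rho 0.7: 200 × 0.51 = 102
- rho 0.8: 200 × 0.36 = 72

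**The case against.** The case on the other side has real force.

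- **Intent beyond single compounds.** A reader might infer that hormones are the only answer offered. They are not: Strengths and limitations names them as one route among others, and the aims mention multivariate analysis. An article may leave the choice of mixture method to the full protocol or analysis plan, so the lack of a named method is not itself a fault. What stands is that the growth models the article does fix are single-compound.
- **Purpose of the hormones.** A reader might infer that hormones are meant to remove co-exposure and fail at it. Effect biomarkers brings them in for mixture and interaction, not for confounding. The narrower point remains: they cannot separate compounds.
- **Disclosure.** The limitation is partly disclosed, but as mixture and interaction. Confounding between compounds is a separate problem that the text does not reach.
- **Attribution.** A reader might infer that no effect can be attributed to any compound. The documents do not support this, because they give no correlation and the bias vanishes at 0. Only for the DEHP metabolites does the article itself show a shared origin, and even there it gives no correlation.
- **Scope.** A reader might extend the quartile criticism to behaviour, or assume the lowest quartile is the reference. Quartiles are stated only for growth, and no reference category is named.
- **Precision.** Adjustment is costly. With over 300 pairs and 40% complete sample sets, about 300 × 0.40 = 120 children are complete now; at rho 0.7 that is the information of 120 × 0.51 = 61. This argues against making adjusted models decisive, not against reporting them.

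**Conclusion.** The point holds in a limited form, as an inexpensive improvement and not as a flaw that invalidates the plan. As specified, the growth models leave confounding by correlated compounds uncontrolled, apart from whatever fish intake may remove, and hormones around birth do not address it. A single-compound association should therefore not be read as specific to that compound without further evidence.

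The bias is nil at rho 0, small at 0.3 if r² is 0.05, and serious from about 0.5, where an inert compound is declared significant in about 20% to 41% of cohorts.

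These figures rest on an assumed rho, one wholly inert and one causal compound, the article's two r² values, n = 200, one BMI measurement with no covariates, and compounds measured without error. The planned repeated-measures models would give somewhat different rates. With measurement error, adjustment would remove less of the bias than shown.

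**What to change.** - Keep the single-compound models as the primary analysis.
- Analyse the three DEHP metabolites as one summed exposure. This reflects their common parent; it is not a co-exposure adjustment.
- Add secondary, mutually adjusted models for cord-blood compounds, for example PCB-153 with DDE and HCB, and PFOS with PFOA.
- Add one joint-mixture analysis for BMI (for example quantile g-computation) that covers compounds across groups, since models within a group leave correlation between groups untouched.
- Report the correlations between compounds, so that readers can judge where the problem is material.
- Where the adjusted estimate differs materially from the single-compound one, describe the single-compound result as not compound-specific.
- Describe the hormones as possible mediators, not as a means of telling compounds apart.

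This costs a few extra models on measurements already planned. The price is wider intervals, and in three-compound models the loss is at least as large as the pairwise figures suggest. The added models should therefore be secondary and should not be a condition for reporting a single-compound result.
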